#### Operational definition of pneumonia

1. Hospitalised cases of pneumonia – J10-J12 (viral) and J13-J18 (bacterial) [21]

2. Health centre diagnosed and treated pneumonia – X-ray confirmed.

### Primary outcomes for exercise intervention

Walking capacity (distance walked in six minutes) 24 months after initiation of the intervention.

### Secondary outcomes

Body mass index [BMI weight (kg)/height (m)^2^] as a measure of potential interaction between the two interventions.

Incidence of acute respiratory infection.

Measure of self-reported health status (Short-Form 36).

Measure of depression (GDS-15).

Self-reported incidence of chronic diseases (diabetes, hypertension, coronary heart disease, stroke, heart failure, arthritic disease) from baseline to 24 months after the initiation of the intervention.

Physical and functional limitations.

Self reported productive activity in the household and community.

Self-reported incidence of falls from six months before the start of the study to 24 months after the initiation of the intervention.

Self-reported incidence of fracture from 12 months before the start of the study to 24 months after the initiation of the intervention.

Blood pressure.

Anthropometry (waist circumference, triceps skin-fold thickness, mid-arm circumference, calf circumference, hand-grip strength.

Timed up-and-go assessment.

Blood indicators of cardiovascular disease risk and insulin resistance (in a sub-sample).

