## Data collection

### Baseline data collection in the original 20 clusters

At the baseline visit, participants were interviewed by project field staff in their local community centre. Participants unable to attend their local community centre were interviewed in their homes by project field staff.

The following information has been collected:

1. Socio-demographic and economic characteristics: standardised questionnaire on family membership, education, marital status, household amenities and tasks, work history (paid and voluntary), contact with family members and help given to them, feelings about age, smoking history and alcohol use. These have been collected in order to help characterise the study population and as predictors of current and future health status.

2. Self-reported health status: the short-form 36 health survey (SF-36) [24] which is well validated for use among adults.

3. Depression: the 15-item Geriatric Depression Scale (GDS 15) [25] will be used to assess the affective state of participants. The GDS 15 is quick and easy to administer and has been validated for use in Chile [26].

4. Self-reported presence of the following medically-diagnosed diseases: pneumonia, diabetes, hypertension, coronary heart disease, stroke, heart failure.

5. Self-reported hospitalization within the previous 12 months as a measure of frailty.

6. Self-reported incidence of falls within the previous 6 months and fractures, and 20 year recall of hip and wrist fracture.

7. Self-reported medications currently being taken on a daily basis.

8. Self-reported health service utilization to assess direct and indirect costs borne by participants.

9. Self-reported frequency of consumption of selected food groups.

10. Self-reported attendance at existing physical exercise classes.

All participants will then be given a further appointment to attend a local community centre a few days later where the following information will be collected by project field staff:

1. Anthropometry: weight; height; arm, waist, hip and calf circumferences; triceps skin-fold thickness; knee height; wrist width; hand-grip strength.

2. Blood pressure measurement: two measurements under sitting conditions separated by five minutes, using a sphygmomanometer.

3. Timed up-and-go: the time taken for a participant to rise from a chair without arm supports, walk three meters, turn around and return to sit on the chair, which is a good marker of mobility among older people.

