### Data collection at 12 months in original 20 clusters

All study participants will be interviewed by project field staff in their local community centre, or visited in their homes, 12 months after their baseline visit. The following information will be collected:

1. Self-reported health status: SF36 as at baseline.

2. Depression: GDS15 as at baseline.

3. Cognitive health: MMSE as at baseline and clock-drawing test on random sub-sample

4. Self-reported history of incidence of pneumonia, diabetes, hypertension, coronary heart disease, stroke, heart failure in the previous 12 months.

5. Self-reported history of falls and fractures in the previous 12 months.

6. Self-reported health service utilization: as at baseline.

7. Compliance with the interventions: short series of open and closed questions regarding uptake and utilization of the interventions.

8. Anthropometry: selected anthropometric measures as at baseline.

9. Blood pressure measurement: as at baseline.

10. Timed up and go: as at baseline.

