### Data collection at 24 months in the original 20 clusters

A final evaluation of all study participants will be carried out after 24 months of intervention. Study participants will be invited to their local community centre, or visited in their homes, and assessed for:

1. Selected socio-demographic characteristics and productive social activity: as at baseline.

2. Depression: GDS15 as at baseline.

3. Self-reported health status: SF36 as at baseline.

4. Cognitive function: as at 12 months.

5. Self-reported presence of medically-diagnosed diseases: as at baseline.

6. Self-reported hospitalization: as at baseline.

7. Self-reported incidence of falls or fractures in the previous 12 months.

8. Self-reported medications currently being taken on a daily basis: as at baseline.

9. Self-reported health service utilization: as at baseline.

10. Compliance with the interventions: as at 12 months.

All participants will then be given an appointment to attend a local community centre where the following information will be collected by project field staff:

1. Anthropometry: as at baseline.

2. Blood pressure measurement: as at baseline.

3. Timed up-and-go: as at baseline.

4. 6 minute walk: as at baseline.

Information on incidence of pneumonia will be collected for 24 months of intervention (including two winter seasons); after this, routine clinic information on pneumonia incidence will be collected on study participants for a further 6 months.

The sub-sample of 120 participants per study arm will be asked for new blood samples collected under fasting conditions, as at baseline.

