### Data analysis

Data analysis will be conducted by statisticians at INTA and LSHTM who will be blind to the treatment allocation. The statisticians will prepare interim analyses for the Data Monitoring Committee as required. The interim analyses will focus on safety aspects of the interventions.

At the end of the interventions, primary analyses will be carried out based upon the groups as randomised ("intention to treat"). Results will be presented as appropriate effect sizes with a measure of precision (95% confidence intervals). All analyses will take account of the clustered design. Covariates will be adjusted for in the analysis as necessary. Further exploratory analyses will be based on those participants who fully follow the various treatment protocols ("per-protocol analyses").

Using the results of the trial and the costing information collected, the incremental cost-effectiveness of the interventions will be evaluated. Sensitivity analyses will be performed to assess the robustness of the findings to changes in key economic and epidemiological parameters. This approach will facilitate discussions about the generalisability of the results to other parts of Chile and beyond.

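### The falls and fracture outcomes are defined over windows that open 6 and 12 months before the study, so 20% and 33% of the outcome period precedes any intervention

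*Protocol article*

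**What the plan says.** The *Secondary outcomes* section of the protocol article gives a time window for three self-reported incidence outcomes:

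- Falls: "Self-reported incidence of falls from six months before the start of the study to 24 months after the initiation of the intervention".
- Fracture: "Self-reported incidence of fracture from 12 months before the start of the study to 24 months after the initiation of the intervention".
- Chronic diseases: "from baseline to 24 months after the initiation of the intervention".

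The data come from three interviews in the original 20 clusters:

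- Baseline: "Self-reported incidence of falls within the previous 6 months and fractures, and 20 year recall of hip and wrist fracture".
- 12 months: "Self-reported history of falls and fractures in the previous 12 months".
- 24 months: "Self-reported incidence of falls or fractures in the previous 12 months".

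The *Data analysis* section gives no rule specific to falls or fractures. It says that "primary analyses will be carried out based upon the groups as randomised" and that "Covariates will be adjusted for in the analysis as necessary". It does not say that pre-study events are set aside from the outcome.

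**The concern.** A fall or fracture that happened before the intervention began cannot have been prevented by it. It is a baseline characteristic. Including it in the outcome has two consequences. On a ratio or proportion scale it adds the same background to both arms and so weakens the contrast. It also carries any difference between arms in prior falls or fractures straight into the estimated effect.

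The second consequence matters more here than in an individually randomised trial. The *Recruitment of participants* section says that clusters were allocated before participants were identified and that the information sheet named the intervention on offer. It acknowledges that this order can produce recruitment bias. People who accept an exercise programme may differ in their fall history from people who accept a control condition.

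The early start is not a habit of the whole list, because the chronic disease outcome starts at baseline. Nor is the pre-study period needed: the two follow-up interviews, each looking back 12 months, together cover the 24 months on study.

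**Working it through.** The article gives no event rate, effect size or power for falls or fractures, so there is no figure of its own to reproduce. The check uses the stated windows.

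**Step 1. Pre-study share.** Taking the start of the study and the initiation of the intervention as the same date:

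- Falls: 6 + 24 = 30 months; 6/30 = 20% pre-study.
- Fractures: 12 + 24 = 36 months; 12/36 = 33% pre-study.

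**Step 2. Rate ratio on pooled events.** Assume a constant event rate, equal pre-study rates in the two arms, and a true on-intervention rate ratio RR. With *pre* the number of pre-study months:

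observed ratio = (pre + 24 × RR) / (pre + 24)

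| Assumed true RR | Falls: (6 + 24 RR)/30 | Fractures: (12 + 24 RR)/36 |
|---|---|---|
| 0.50 | 18.0/30 = 0.60 | 24.0/36 = 0.67 |
| 0.70 | 22.8/30 = 0.76 | 28.8/36 = 0.80 |
| 0.80 | 25.2/30 = 0.84 | 31.2/36 = 0.87 |
| 0.90 | 27.6/30 = 0.92 | 33.6/36 = 0.93 |

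Under these assumptions the apparent relative reduction is 24/30 = 80% of the true one for falls and 24/36 = 67% for fractures.

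**Step 3. Other effect measures.**

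- *Any event (yes/no).* With probability 1 − exp(−rate × time), an assumed 0.3 events per year and RR 0.70, the clean 24-month risk ratio is 0.76. It becomes 0.82 with the falls window and 0.87 with the fracture window. The risk difference goes from 0.108 to 0.093 and 0.080.
- *Difference in mean counts.* The pre-study terms cancel in expectation, which leaves 24 × rate × (1 − RR) whatever *pre* is. The size is unchanged; only the variance grows.

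**Step 4. Cost in information.** Ignoring clustering, with 80% power at an assumed RR of 0.70, the events needed rise from 247 to 417 (falls) or 631 (fractures). This overstates the cost, because the longer window also supplies more events. In month-equivalents summed over the two arms, the totals are:

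- clean window: 24 + 16.8 = 40.8;
- falls window: 30 + 22.8 = 52.8;
- fracture window: 36 + 28.8 = 64.8.

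The net inflation in participants is about (417/247)/(52.8/40.8) = 1.30 for falls and (631/247)/(64.8/40.8) = 1.61 for fractures. The any-event calculation at a low assumed rate (0.02 per year) agrees: 3768 per arm becomes 4901 (ratio 1.30) or 6046 (ratio 1.60).

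**Step 5. Pre-study imbalance.** If the ratio of pre-study rates between arms is k instead of 1:

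observed ratio = (pre × k + 24 × RR) / (pre + 24)

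This is a weighted average of k and RR. The observed ratio lies above RR when k > RR and below it when k < RR. Imbalance can therefore hide a benefit or exaggerate one.

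**The case against.** The strongest reply is that the article lists periods of measurement and nowhere says that events before and after the start are summed. The reports come from three separate interviews, and the six months in the falls line match the baseline recall of falls exactly. The line may simply mean a baseline value plus follow-up. How the baseline reports enter the model is a detail that an article can leave to the full protocol or SAP, so the absence of a named covariate is not a fault.

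Much of this stands. Pooling is not stated, and the figures in the working are conditional on it. The data can be separated at analysis, so nothing is lost for good. What does not stand is that the wording is harmless. The windows are explicit, they differ from the baseline start used for chronic diseases in the same list, and nothing in the article removes the pre-study events. Anyone who builds the outcome as defined would count them. The match with the baseline recall also fails for fractures, where the baseline item gives no 12-month period.

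A reader might go further and infer three things that the article does not support:

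- That any effect is necessarily pulled toward the null. That depends on the effect measure and on balance before the study.
- That these are key outcomes of the exercise programme. They are two of thirteen secondary entries, assigned to neither intervention, and appear in no study hypothesis or sample size calculation.
- That the windows distort the cost analysis. The *Costing data* section names fractures but not falls, and relies on service-use data and ministry reference prices, not on these self-reports.

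**Conclusion.** The definitions should be corrected. As written, 20% of the falls window and 33% of the fracture window precede any intervention.

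The effect on the estimate is conditional. With pooled events, constant and balanced pre-study rates and a rate ratio, 0.80 would be reported as 0.84 or 0.87, and 0.70 as 0.76 or 0.80. An any-event proportion would also be attenuated. A difference in mean counts would only lose precision. Pre-study imbalance, plausible under this recruitment order, could move the result either way, so the net direction cannot be stated in advance. The true ratios and event rates used are assumptions, and clustering is ignored.

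The consequence is moderate: these are secondary outcomes, the trial is not sized on them, and the data collected allow a clean definition.

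**What to change.** Define falls and fracture as events from initiation of the intervention to 24 months, taken from the 12-month and 24-month interviews. State that the baseline falls history and fracture history serve only as baseline covariates. That adjustment is worth having in its own right: starting the window later removes pre-study events from the outcome, but not a lasting difference in risk between the people recruited to each arm.

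Also state the recall period of the baseline fracture item, since only the 20-year recall of hip and wrist fracture is given.

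The cost is two lines of outcome definition and one of clarification. No new data are needed, because the two follow-up interviews, held on schedule, already cover the 24 months.

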### Sample size calculations

#### Original sample size calculations

Using data available at the initial planning of the study, the required sample size was calculated based on the hypothesised effect sizes, and the likely rates of participant drop-out for the different outcomes. It was assumed that there would be no important interactions between the interventions for the primary outcomes, and that there might be an interaction for the BMI outcome.

For the pneumonia incidence outcome, the sample size was calculated based on a comparison of health centre catchment areas with and without the nutrition intervention. The nutrition intervention was originally planned to be made available to all eligible adults in the health centre catchment area and it was originally estimated that 10 health centres providing the nutritional supplement and 10 control health centres would be sufficient to detect a 33% reduction in pneumonia incidence in the health centre catchment area. This size of reduction was based on the observed difference in rates of pneumonia between high and low income groups in Santiago. In order to detect this effect size with 10 clusters per arm, p < 0.05 and 90% power and with a coefficient of variation [22] of 19%, 704 person-years of follow-up per cluster were required i.e. 352 participants per cluster over 2 years. Therefore the minimum 400 available participants per cluster were defined as more than adequate. The centralised system for registration of pneumonia cases ensured that loss to follow-up would not affect the capacity of the study to assess this outcome.

For the walking capacity outcome, the sample size was calculated based on a comparison of health centres with and without the physical exercise intervention. The mean change and variability in walking capacity and the coefficient of variation (78%) was assumed to be the same as observed in the control arm of a recent trial among older people in Santiago [23]. In addition it was assumed that the impact of the intervention would be half that observed after 18 months in the exercise arms of the same trial i.e. 13% (the trial had more intensive support for participants than the current study) [23]. In order to detect this effect size with p < 0.05, 90% power and 10 clusters per arm, 162 person-years of follow-up per cluster were required i.e. 81 participants per cluster over 2 years. Allowing for 20% drop-out, a sample of 100 participants from each of 10 health centres with equal numbers of controls was defined as sufficient.

As there may be an interaction between the interventions for the BMI outcome, the necessary sample size for this outcome was calculated based on a comparison of health centres with all combinations of both interventions. The mean and variability of BMI and the coefficient of variation (10%) were taken to be the same as observed in the control arm of the recent trial in Santiago [23]. In order to detect a 0.5 unit mean change in BMI, with p < 0.05, 90% power and 5 clusters per arm 64 person-years of follow-up per cluster were required i.e. 32 participants per cluster over 2 years. Therefore, the 4 groups of 500 participants (100 from each of 5 health centres) sampled for the walking capacity outcome would be more than adequate to explore an interaction between the two interventions for this outcome.

The sample size was therefore defined as a total of 2000 individuals drawn from 20 health centres.

A sub-sample of randomly selected participants was assessed for blood indicators of cardiovascular risk and insulin resistance under fasting conditions. Assuming a coefficient of variation of 10%, 80% power, p < 0.05, and 20% drop-out a sample of 120 individuals per study arm was defined as sufficient to detect a 0.5SD change in these indicators.

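### The walking-capacity sample size is derived in person-years and halved for two years of follow-up, so the printed derivation does not support 90% power for an outcome measured once, at 24 months

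*Protocol article*

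**What the plan says.** The walking calculation is in the protocol article under Original sample size calculations. Its inputs are:

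- Design: "In order to detect this effect size with p < 0.05, 90% power and 10 clusters per arm".
- Variability, taken from a control arm of an earlier Santiago trial: "The mean change and variability in walking capacity and the coefficient of variation (78%) was assumed to be the same".
- Effect, in per cent: "half that observed after 18 months in the exercise arms of the same trial i.e. 13".
- Result: "162 person-years of follow-up per cluster were required i.e. 81 participants per cluster over 2 years".
- Enrolment: "Allowing for 20% drop-out, a sample of 100 participants from each of 10 health centres with equal numbers of controls". This number then fixes the 2000 participants in the original 20 clusters.

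The BMI calculation in the same section has the same form, with 5 clusters per arm: "64 person-years of follow-up per cluster were required i.e. 32 participants per cluster over 2 years".

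The exercise outcome is defined as "Walking capacity (distance walked in six minutes) 24 months after initiation of the intervention". The walk test is done at baseline and again at the end ("4. 6 minute walk: as at baseline" in the 24-month list). It is not in the 12-month list.

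**The concern.** The pneumonia calculation in the same section also goes from person-years to participants (704 to 352). That is legitimate, because pneumonia is an incidence rate and each further year of observation adds information. The walking and BMI calculations copy this layout for continuous measurements. A participant followed for two years supplies one 24-month walking distance, not two, so dividing a required number of observations by two has no basis.

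Walking capacity is a primary outcome, and its calculation sets the 100 participants per cluster. The later revision of the sample size concerns pneumonia only, and the eight added clusters collect data for that outcome only. Nothing later in the article repairs the walking figure.

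**Working it through.** **Inputs.** From the article: 90% power, p < 0.05, 10 clusters per arm, CV 78%, effect 13%, 20% drop-out. Assumed: a two-sided test, and a CV and effect relative to the same mean. No ICC is given for walking. The only ICC in the article is 0.001, for pneumonia, in the revised calculation.

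**Step 1. Try to reproduce the stated figure.** With f = (1.96 + 1.2816)² = 10.507 and 78% read as individual SD/mean:

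- n per arm = 2 × 10.507 × 0.78² / 0.13² = 757, or 75.7 persons per cluster with no clustering.
- This is neither 81 nor 162, though it is near 81.
- With an ICC ρ, m = 75.7(1 − ρ)/(1 − 75.7ρ). Borrowing ρ = 0.001 gives m = 81.8, close to 81 as a head-count.
- Conversely, 81 × 10 = 810 persons leaves a design effect of 810/757 = 1.07, so ρ ≈ 0.07/80 ≈ 0.0009.

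The article does not say which of 162 and 81 came out of the formula, so both are carried forward.

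**Step 2. Completers.** 100 enrolled less 20% leaves 80 per cluster.

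**Step 3. If 162 was the number of persons required.** Enrolment to retain 162 would be 162/0.8 = 203 per cluster, against 100. Power at 80 is Φ(3.2415 × √R − 1.96), where R = [80/(1 + 79ρ)] / [162/(1 + 161ρ)].

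| ICC assumed in the calculation | Power at 80 |
|---|---|
| 0 | 62.5% |
| 0.001 | 65.6% |
| 0.01 | 78.5% |
| 0.05 | 86.9% |

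For example, at ρ = 0: 3.2415 × √(80/162) − 1.96 = 0.318, and Φ(0.318) = 0.625.

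**Step 4. If 81 was the number of persons, with an individual CV of 78%.** Power at 80 is Φ(√(n_eff/2) × 0.13/0.78 − 1.96), where n_eff = 800/(1 + 79ρ).

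| Assumed ICC | Design effect | Power at 80 |
|---|---|---|
| 0 | 1.000 | 91.5% |
| 0.001 | 1.079 | 89.4% |
| 0.005 | 1.395 | 80.6% |
| 0.01 | 1.79 | 70.2% |
| 0.02 | 2.58 | 54.6% |

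These use the normal approximation. A t-test on cluster means with 18 degrees of freedom gives 88.3% at ρ = 0.

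**Step 5. BMI.** Undoing the halving leaves 64 persons per cluster. The article plans 100, or about 80 if the walking drop-out of 20% also applies. If 64 gives 90% power, 80 gives Φ(3.2415 × √(80/64) − 1.96) = 95.2% at ρ = 0. The same formula with design effects gives 91.3% at ρ = 0.05.

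**The case against.** The strongest reply is that person-years is only a wrong label. The stated inputs give about 76 persons per cluster without clustering, and 81.8 with the pneumonia ICC. On that view 81 was the head-count all along and 162 was obtained by doubling it, so the design loses nothing. This is plausible and cannot be excluded. It does not rescue the printed derivation, because the 90% then depends on almost no clustering of walking capacity. The article neither states nor justifies that.

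A second reply is that the 78% may describe the *change* in walking distance. The standard formula is c = 1 + f × [2σ²/m + k²(μ₀² + μ₁²)]/(μ₁ − μ₀)². As an illustration, take k = 0.78 between clusters, a 13-point difference, an individual SD of change of 15 to 20% of baseline distance, and m = 80. It gives about 5 to 8 clusters per arm if the control change is between −5% and 0, about 10 at +2%, and 14 to 15 at +5%. These inputs are assumed, since the article gives neither the control change nor the SD. The point stands that some readings fit the planned 10 clusters.

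A reader might therefore infer from the unit error that no interpretation reaches 90% power. The documents do not support that: Step 4 gives about 92% at ICC 0 and 89% at 0.001. Nor should the 78% be forced into a between-cluster CV on the same mean as the 13% effect. That would need about 860 clusters per arm, and the text does not impose it.

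Finally, the 2000 participants had been recruited by December 2005. That limits what can be changed, but it does not make the stated power correct.

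**Conclusion.** The conversion is invalid for an outcome with one 24-month value per person, and the stated 90% power for walking capacity is not established by the derivation shown. With about 80 completers per cluster, power is roughly 62% to 87% if 162 persons were required (ICC 0 to 0.05). If 81 persons were required with an individual-level CV of 78%, it runs from about 92% down to 55% (ICC 0 to 0.02). All ICCs are assumptions, and the documents do not settle which case applies. The finding is unsupported power, not a demonstrated shortfall.

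For BMI a reader might infer that the planned sample is too small. The unit error does not show this: the unhalved 64 is still below about 80 completers, with 91% to 95% power on the article's own figure. Only the unit needs correcting. Reading the 10% as SD/mean with an assumed mean BMI of 25 to 30 would give 105 to 151 persons per cluster before clustering. But the article gives no mean BMI and does not define the 10%, so this is a reason to define the term, not evidence of a deficit. Selected anthropometry at 12 months may also include BMI, though no repeated-measures use is stated.

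**What to change.** - State both requirements as numbers of participants with a 24-month measurement, and delete the person-year conversions (162 to 81, and 64 to 32).
- Say whether the 78% and 10% coefficients of variation are individual-level or between-cluster, and of which quantity. Give the mean and SD used.
- Restate the walking power for about 80 completers in 10 versus 10 clusters, with an explicit between-cluster variance or a range of ICCs.
- Specify adjustment of the walking analysis for the baseline six-minute walk, which is already collected. The Data analysis section leaves covariate adjustment open, so this makes it definite and can recover precision.

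The cost is a recalculation and revised wording. No extra participants or measurements are needed. The stated power for walking may become less favourable.

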**Methods:**

The study has been conceptualised as a public health programme effectiveness study and has been designed as a 24-month factorial cluster-randomised controlled trial conducted among 2800 individuals aged 65.0–67.9 years at baseline attending 28 health centres in Santiago. The main outcomes are incidence of pneumonia, walking capacity and change in body mass index over 24 months of intervention. Costing data (user and provider), collected at all levels, will enable the determination of the cost-effectiveness of the two interventions individually and in combination. The study is supported by the Ministry of Health in Chile, which is keen to expand and improve its national programme of nutrition for older people based on sound science-base and evidence for cost-effectiveness.

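### The BMI requirement of 32 participants per cluster does not follow from the stated 10% coefficient of variation of BMI, so the printed inputs do not support calling the sample more than adequate for an interaction

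*Protocol article*

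**What the plan says.** All of this stands in the protocol article, under Original sample size calculations, unless another place is named.

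- Target: "In order to detect a 0.5 unit mean change in BMI, with p < 0.05, 90% power and 5 clusters per arm".
- Variability: "The mean and variability of BMI and the coefficient of variation (10%) were taken to be the same as observed in the control arm" of an earlier Santiago trial. No mean BMI, SD of BMI, SD of BMI change or intra-cluster correlation is printed for this outcome. The text does not say whether the 10% is between people or between clusters.
- Result: "64 person-years of follow-up per cluster were required i.e. 32 participants per cluster over 2 years".
- Conclusion: "the 4 groups of 500 participants (100 from each of 5 health centres") recruited for the walking outcome are judged more than sufficient to explore an interaction between the two interventions on BMI.
- Drop-out: 20% is allowed for in the walking paragraph, and BMI uses the same participants, so 80 of 100 per cluster would be retained.
- Outcome: the abstract names "change in body mass index over 24 months of intervention" among the main outcomes. The third of the three hypotheses, which the Design section calls primary, is that supplement plus exercise will not induce weight gain as measured by BMI. The Secondary outcomes list also includes BMI, as a measure of potential interaction.

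**The concern.** The effect to be detected is a change in BMI, but the variability cited is that of BMI itself. The walking paragraph, by contrast, refers to the mean change and its variability. When the 10% is used as printed, the required number per cluster comes out far above 32 on one reading and unattainable on the other.

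This matters because the third hypothesis asserts no weight gain. For a hypothesis of that form, low power works in favour of the expected conclusion. A stated 90% power and a comfortable surplus of participants would encourage a reader to take a null BMI result, or a null interaction, as confirmation.

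**Working it through.** **Inputs from the article.** Difference d = 0.5 units; alpha 0.05 (sidedness not stated, two-sided taken); power 90%; 5 clusters per arm; 10% coefficient of variation; 32 per cluster stated; 100 per cluster planned, 80 after 20% drop-out. **Assumed:** mean BMI, which the article does not give. The range 20 to 32 is used to test whether 32 can be reproduced, and 25 to 30 to illustrate power.

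Constant: f = (1.960 + 1.282)² = 10.507.

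**1. Trying to reproduce 32, with 10% as between-person SD/mean and no clustering.**
For a two-arm contrast, n per arm = 2f·SD²/d². With 5 × 32 = 160 per arm, the largest SD giving 90% power is √(160 × 0.25 / (2 × 10.507)) = 1.38. At a 10% coefficient this is a mean BMI of 13.8. Counting only 4 effective clusters (the usual correction of one extra cluster per arm) lowers it to 1.23, a mean of 12.3. One-sided alpha raises the 13.8 only to 15.3.

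In the other direction:

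| Assumed mean BMI | SD | Required per arm | Per cluster |
|---|---|---|---|
| 20 | 2.0 | 337 | 67 |
| 25 | 2.5 | 526 | 105 |
| 27 | 2.7 | 613 | 123 |
| 30 | 3.0 | 757 | 151 |
| 32 | 3.2 | 861 | 172 |

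No mean from 20 to 32 gives 32 per cluster. At mean 27, lowering power to 80% still requires 92, and one-sided alpha still requires 100.

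**2. Trying to reproduce 32, with 10% as between-cluster SD/mean.**
The pneumonia paragraph sets its own figure, "with a coefficient of variation [22] of 19" per cent, beside the number of clusters, which makes this reading natural. Even with unlimited participants, 90% power requires a between-cluster SD of at most √(5 × 0.25 / (2 × 10.507)) = 0.24, or √(4 × 0.25 / (2 × 10.507)) = 0.22 with the extra-cluster correction. Ten per cent of 20 to 32 is 2.0 to 3.2 units, so no number per cluster suffices.

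**3. What would give 32.**
If the analysed quantity is change in BMI, step 1 shows that an SD of change of 1.23 to 1.38 yields 32. From a level SD s, the SD of change is s·√(2(1 − r)), so r = 1 − (SD of change / s)²/2. At s = 2.5 this gives r = 0.85 to 0.88, and at s = 3.0 r = 0.89 to 0.92. Treating the 10% as a between-cluster coefficient of a small mean change (0.25 units assumed) with SD of change 1.2 also works: n = 2 × 1.2² / [4 × 0.25/10.507 − 0.01 × (0.25² + 0.75²)] = 32.4. Both routes need an SD of change that the article does not state.

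**4. Power at the planned size, on an unadjusted comparison of levels.**
With 5 × 80 = 400 retained per arm and no clustering:

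- Two-arm contrast, power = Φ(0.5 / (SD·√(2/400)) − 1.96): 81% at SD 2.5 and 65% at SD 3.0.
- Interaction contrast (difference of differences over four arms, twice the variance), power = Φ(0.5 / (SD·√(4/400)) − 1.96): Φ(2.00 − 1.96) = 52% at SD 2.5 and Φ(1.667 − 1.96) = 38% at SD 3.0.

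**5. Power at the planned size, on change.**
Take SD of change 1.3 and 80 retained per cluster. The interaction contrast has SE 1.3 × √(4/400) = 0.13 and power Φ(3.85 − 1.96) = 97% with no clustering. With an assumed intra-cluster correlation of 0.02 the design effect is 1 + 79 × 0.02 = 2.58, the SE is 0.209, and power is Φ(2.39 − 1.96) = 67%. Adequacy therefore turns on two figures that the article does not give.

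**The case against.** The strongest reply is that the powered quantity is a mean change in BMI. A baseline-to-24-month correlation near 0.9 would be enough to give 32, and then 100 per cluster would be ample for a two-arm contrast. Even with a level SD of 2.5 to 3.0, a change-score analysis reaches 90% power for a two-arm contrast at 80 retained if the correlation is about 0.62 to 0.74 (SD of change at most 2.18, no clustering). This stands. It rules out saying that 32 could never be obtained, or that the adequacy claim is false.

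The following parts also stand:

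- The power figures of 65% to 81% rest on an assumed mean of 25 to 30. On the between-person reading, a mean of 21.8 or less would give 90% power at 80 per cluster for two arms.
- A between-cluster SD of 2 to 3 BMI units mainly suggests that this reading was not intended. It is not evidence that the trial has almost no power.
- The article is condensed, and leaving an SD to a fuller document is not itself a fault.
- BMI appears in the secondary outcome list, the total of 2000 was driven by walking, and the analysis section commits to 95% confidence intervals, which would show imprecision.

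The mismatch remains. The article does print a variability input, ties it to BMI rather than to its change, and derives from it a size and a power that it does not yield. The replies about change scores also concern a two-arm contrast, whereas the conclusion drawn is about an interaction, which has twice the variance.

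**Conclusion.** The point holds in a limited form. The stated 32 per cluster does not follow from a 10% coefficient of variation of BMI on either meaning of the term, at any assumed mean from 20 to 32. It can be reached only with an SD of change of about 1.2 to 1.4, which is not stated. The claim that the sample is more than adequate for an interaction is therefore unsupported by the printed inputs.

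A reader might go further and infer that the trial is underpowered for BMI. The article does not establish that. The 81% to 65% (two arms) and 52% to 38% (interaction) at 80 retained per cluster apply to an unadjusted comparison of levels, with an assumed mean of 25 to 30 and no clustering. A change or baseline-adjusted analysis could be adequate. For the interaction, that depends on both the SD of change and the between-cluster variance.

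**What to change.** Under Original sample size calculations, redo the BMI paragraph for the outcome to be analysed (24-month change, or 24-month BMI adjusted for baseline) and for the contrast claimed, the interaction. Use a between-person SD and a between-cluster SD of BMI change, in BMI units, estimated blind to arm from the baseline and 12-month anthropometry of the 20 original clusters. Since these cover 12 months, state how they are carried to 24.

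Replace the 32 per cluster, the 90% power and the adequacy statement with the resulting power, or the minimum detectable BMI difference, for 5 clusters per arm and 80 retained per cluster. State which kind of coefficient the 10% was.

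The cost is one blinded variance estimate on measurements already scheduled, plus revised wording, with no change in enrolment. The drawback is that the stated detectable difference may turn out larger than 0.5 units.
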